# Effectiveness of a nutrition education package in improving feeding practices, dietary adequacy and growth of infants and young children in rural Tanzania: rationale, design and methods of a cluster randomised trial

**DOI:** 10.1186/1471-2458-14-1077

**Published:** 2014-10-16

**Keywords:** Nutrition education, Complementary feeding, Growth, Tanzania, Cluster randomised trial, Process evaluation, Intervention mapping, Theory of planned behaviour

## Abstract

**Background:**

Strategies to improve infant and young child nutrition in low- and middle- income countries need to be implemented at scale. We contextualised and packaged successful strategies into a feasible intervention for implementation in rural Tanzania. Opportunities that can optimise delivery of the intervention and encourage behaviour change include mothers willingness to modifying practices; support of family members; seasonal availability and accessibility of foods; established set-up of village peers and functioning health system. The primary objective of the study is to evaluate the effectiveness of a nutrition education package in improving feeding practices, dietary adequacy and growth as compared to routine health education.

**Methods/Design:**

A parallel cluster randomised controlled trial will be conducted in rural central Tanzania in 9 intervention and 9 control villages. The control group will receive routine health education offered monthly by health staff at health facilities. The intervention group will receive a nutrition education package in addition to the routine health education. The education package is comprised of four components: 1) education and counselling of mothers, 2) training community-based nutrition counsellors and monthly home visits, 3) sensitisation meetings with health staff and family members, and 4) supervision of community-based nutrition counsellors. The duration of the intervention is 9 months and infants will be recruited at 6 months of age. Primary outcome (linear growth as length-for-age Z-scores) and secondary outcomes (changes in weight-for-length Z-scores; mean intake of energy, fat, iron and zinc from complementary foods; proportion of children consuming 4 or more food groups and recommended number of semi-solid/soft meals and snacks per day; maternal level of knowledge and performance of recommended practices) will be assessed at baseline and ages 9, 12 and 15 months. Process evaluation will document reach, dose and fidelity of the intervention and context at 8 and 15 months.

**Discussion:**

Results of the trial will provide evidence of the effectiveness of the nutrition education package in community settings of rural Tanzania. They will provide recommendations for strengthening the nutrition component of health education in child health services.

**Trial registration:**

ClinicalTrials.gov Identifier: NCT02249754, September 25, 2014.

**Electronic supplementary material:**

The online version of this article (doi:10.1186/1471-2458-14-1077) contains supplementary material, which is available to authorized users.

## Background

Undernutrition is an underlying cause of more than one-third of global deaths in children below the age of 5 years. It is also associated with growth faltering (i.e. deficit in height or stunting), micronutrient deficiencies, delayed cognitive development and morbidity [1]. Stunting and micronutrient deficiencies are significant health problems among infants and young children in Tanzania. Prevalence of stunting among children aged 6–59 months in the national surveys of 2005 and 2009/2010 was 37.7% and 42%, respectively [2, 3]. Children in rural areas were more affected than their urban peers (40.5% vs 37.7% in 2005; 44.7% vs 32.1% in 2010). Children living in the southern and central regions of the country were more affected than those living in other regions.

Poor breastfeeding practices, inadequate dietary intake from complementary foods, high rates and repeated episodes of diseases, maternal inadequate nutritional knowledge and household food insecurity have been associated with stunting in Tanzania [4–7]. Overall, only 2 out of 10 Tanzanian children are fed in accordance with the recommended infant and young child feeding (IYCF) practices [3]. Among the breastfed children (6–23 months-old), 61% were given foods from three or more food groups, 39% were fed the minimum number of times, 30% consumed iron-rich foods and 62% consumed vitamin A-rich foods.

A formative research was conducted in one of the central regions with high rates of malnutrition to closely examine feeding practices, diets and nutritional status of infants and young children and guide decisions on improvement. The research was conducted in Dodoma in two phases. The first survey, conducted in 2009 during the post-harvest season, involved 496 households with infants aged 1 to 12 months. The second survey revisited the same households and infants in 2010 during the harvest season. Results of the surveys indicated high prevalence of stunting; 34% in 2009 and 59% in 2010. Morbidity due to acute respiratory illness (ARI) was 64% in 2009 and 57% in 2010. Diarrhoea affected 48% children in 2009 and 37% in 2010. Prevalence of anaemia was high (11 - 60% in 2009; 20 - 75% in 2010). Complementary fluids and foods were introduced at the median age of 3.0 months and 90% of children had received these foods earlier than the recommended age of 6 months. Feeding frequencies (1.7 in 2009 and 2.4 in 2010) were lower than the age-specific World Health Organisation (WHO) recommendations [8]. Portion sizes for different types of relish/sauce were small.

Similar findings in low- and middle- income countries (LMIC) have been documented in rural areas and have progressively worsened throughout the first year of life [9–13]. Systematic reviews of complementary feeding interventions have provided evidence of well adopted feeding practices, improved food recipes, increased dietary adequacy and growth and reduced prevalence of anaemia and morbidity [14–17]. The interventions included a combination of strategies, namely culturally-appropriate group nutrition education, individual counselling, interpersonal communication, home visits and mass media [18–23]. Great impact and sustainability of the interventions were achieved through participatory approaches and community involvement [24–26].

The formative research in Dodoma showed that age-specific, systematic and locally relevant interventions are needed to ensure rural children receive the best possible start in life. To address the nutrition and health situation, intervention strategies were identified and contextualised according to, among other factors, local dietary patterns, meal preparation, food beliefs and preferences, food availability and cost and ability to change attitudes. The strategies were packaged as a nutrition education package. Opportunities that could optimise successful delivery of the package and encourage behaviour change include willingness to modifying some feeding options, seasonal availability and accessibility of foods, established set-up of village peers and existence of health centres and health staff in some villages. This paper describes the rationale, design and methods of a cluster randomised controlled trial to evaluate the effectiveness of a nutrition package in rural Tanzania.

### Objectives and hypothesis

The primary objective of the intervention trial is to implement and evaluate the effectiveness of a nutrition education package in improving infant and young child feeding practices, dietary adequacy and growth. The trial hypothesises that the nutrition education package will be more effective than the routine health education. The primary outcome will be linear growth as assessed by change in length-for-age Z scores. Secondary outcomes will include feeding practices, nutrients intake and level of knowledge on recommended practices. Results of the trial are expected to provide evidence to the effectiveness of the package in community settings and, where appropriate, recommendations to strengthen the nutrition component of health education in child health services.

## Methods/Design

### Development of the nutrition education package

Intervention Mapping and Theory of Planned Behaviour [27, 28] provided the theoretical framework for the design and development of the package and the intervention. The intervention mapping framework integrates theory, empirical findings from the literature and information collected from the target population to develop culturally appropriate and theoretically sound interventions [29, 30]. The framework has been used successfully to develop health behaviour interventions [31, 32]. This study applied consecutively and iteratively the six steps of intervention mapping.

#### Step 1: Needs assessment

Needs assessment involved a literature study on complementary feeding strategies in LMIC, review of secondary data on child health and the formative research conducted in 2009 and 2010 in the study area. Key informant interviews, focus group discussions, food market surveys and household surveys were conducted to obtain in-depth insight into the nutrition and health situation of infants and young children, community and household factors, parents’ motivations and behaviours that facilitate and constrain infant and young child feeding and health.

#### Step 2: Identifying intervention performance and change objectives

Results from *Step 1* were used to identify behaviours, motivations, barriers, predisposing and enabling factors associated with inadequate dietary intake, morbidity and poor growth. A conceptual framework illustrating expected behaviours and mediating factors for improvement of child growth was developed (See Additional file 1). Aspects that will be implemented by the intervention are also presented. The overall intervention objective “improve feeding practices, dietary adequacy and growth of infants and young children (6–15 months)” was formulated and divided into sub-objectives and behavioural performance objectives (i.e. target behaviours that have to be accomplished by the target group to achieve the intervention objective). A matrix of intervention objectives and behavioural performance objectives, classifying individual and environmental determinants as mediating mechanisms and modifying conditions was developed (See Additional file 2). Discussions with district health experts and village health committees helped to refine the intervention further.

#### Step 3: Selection of theory-based intervention methods and techniques

Theoretical methods considered to influence changes of performance objectives (i.e. target behaviours) were identified and practical strategies were selected to put the theoretical methods into practice [31]. Systematic reviews [14–16], individual nutrition education and counselling interventions [20, 21] and summary of theoretical methods [31] were used in the selection of existing methods and techniques, and the development of new strategies which fitted our intervention and behavioural objectives. Theory of Planned Behaviour was used as the main focus of behavioural change during the selection of theory-based methods and strategies [33]. The theory has been widely employed in health and nutrition behaviour change studies [28, 34, 35], including infant feeding [36–38]. The theory facilitates an understanding of how behavioural intentions influence actual behaviour change, with skills, abilities and environmental factors acting as important moderators of change.

The theoretical methods were translated into practical strategies and these were related to the levels of the intervention. An example includes a behavioural objective and outcome expectation of “adding mashed animal-source food to infant meals at least 3 times per week would provide nutrients to make a child grow well and offer protection against common illnesses.” A mother will be willing and more likely to apply the recommendation using the following methods and techniques:

the individualisation method to provide opportunities for mothers to have personal questions and concerns about child feeding answered (e.g. what to feed, how to feed) or instructions paced according to individual progress;cognitive skills training with guided practice to influence self-efficacy;tailoring to increase practical knowledge on selection and preparation of new food recipes; andmobilising social support (e.g. trained peers, sensitised family members and health facility staff) to offer encouragement and support, and likely to help the mother to maintain optimal child feeding practices.

#### Step 4: Developing the intervention and pre-testing

The intervention objectives, selected methods and strategies were combined and a nutrition education package was developed. The nutrition education package is composed of four components, namely 1) education and counselling of mothers, 2) training community-based nutrition counsellors and monthly home visits, 3) sensitisation meetings, and 4) supervision of community-based nutrition counsellors. Draft versions of the package were discussed with district health and nutrition experts, village health committees and fine-tuned by the research team. Behavioural change at the individual level is intended for mothers of rural infants aged 6 months through education and counselling sessions and cooking demonstrations. Based on local typical meals, the intervention will promote preparation and consumption of a variety of foods. Behavioural change at the family level will consist of sensitisation meetings with family members of targeted infants. This will help to create a nutrition-promoting environment. At the community level, the intervention will train community-based peers such as village health workers, lay counsellors and resource persons to support mothers and families through home visits. In addition, sensitisation meetings with health facility staff will help to reinforce and support mothers’ behaviour change.

Training and educational resources were developed to support the implementation of the package. These include: 1) Training guide for community-based nutrition counsellors, 2) Manual for community-based nutrition counsellors, 3) Educational plan for mothers, 4) Information booklet for mothers and families, and 5) Counselling cards. The resources contain topics on breast feeding, complementary feeding, selection and preparation of locally available foods, feeding during illness, healthcare-seeking, hygiene and home environment sanitation. In addition to these, resources for nutrition counsellors cover communication skills, behaviour change communication and counselling skills. The developed resources were pre-tested with a convenient sample to assess whether the content and format were realistic, understandable, culturally appropriate, visually appealing and motivating.

#### Step 5: Implementation plan of intervention

The intervention strategy is centred on the child with their mothers as the primary target group. To stimulate lasting behaviour change, ensure continuity, and enhance linkage between communities and health facilities, secondary target groups have been incorporated in the intervention. These include family members (fathers, grandmothers, school-going siblings), community-based nutrition counsellors and healthy facility staff. Supportive structures such as district health management team and village health committees will be consulted regularly to enhance intervention support and feedback.

#### Step 6: Evaluation plan of intervention

The effectiveness of the nutrition education package is evaluated in a cluster randomised controlled trial, whereby villages will be randomly allocated to receive a nutrition education package or routine health education. The intervention group will receive the nutrition education package, whereas the control group will continue to receive routine health education given monthly at health facilities. Children aged 6 months and their families will be recruited and followed up for 9 months. Extensive process evaluation will also be performed to document reach, dose and fidelity of the intervention trial.

### Study setting

The intervention will be conducted in Mpwapwa District in Dodoma Region, central Tanzania. Dodoma is among the regions in the country with the highest prevalence of stunting, 44.4% in 2005 and 56.0% in 2010 [2, 3]. The District has a total population of 304,096 and 67,577 households [39]. The region is predominantly semi-arid, characterised by a short single wet season (November to March) and a long dry season (May to mid-November). Subsistence farming and traditional rearing of animals are the primary economic activities. The district health system makes child health services available through a network of 43 dispensaries, 2 health centres and 1 district hospital. Mpwapwa district is administratively divided into 3 divisions, 18 wards, and 84 villages [39]. A village is the lowest administrative unit and is considered as a geopolitical unit and intact social group. It has a local government authority and committees. Each village usually has two village health workers. They work as volunteers, mainly to assist health facility staff during immunisation and child growth monitoring activities.

### Study design

The intervention trial will use a parallel cluster-randomised controlled trial design (Figure 1) and will be conducted and reported in line with the CONSORT recommendations for cluster randomised trials [40]. Because the intervention will be delivered in community settings and encourage collective participation at household settings, to minimise contamination and facilitate logistical convenience in delivery, the unit of randomisation will be the village. Villages will be randomly assigned to either the intervention or control study groups. The intervention duration will be 9 months. Infants will be recruited when aged 6 months and followed up until they attain 15 months.

**Figure 1 Fig1:**
[figure not shown]
**Trial profile.**

The control group will continue to receive routine health education, a standard government health service for children below the age of five years, offered monthly by health staff at health facilities. Routine health education offers education to mothers during growth monitoring and immunisation contacts. The sessions are usually short (10–15 minutes) and focus on general health issues including child feeding, prevention of diseases such as malaria and importance of immunisations.

The intervention group will receive the nutrition education package in addition to the routine health education. Mothers and caregivers will receive 3 sessions of education and counselling on optimal infant and young child feeding and health, when the child reaches 6 months, 9 and 12 months. Nutrition counsellors will receive training at baseline and the session will be repeated after 6 months. After training, the nutrition counsellors will conduct monthly home visits to counsel and support mothers and their families. Supervisory visits will be conducted by the research team after every 2 months to assess counsellors’ work. Separate sensitisation meetings with families and health staff responsible for child health will be conducted at baseline and meeting will be repeated after 6 months.

### Sampling and randomisation

A village forms a unit of randomisation for the trial, while infants and their parents within the village will form units of observation. Two out of three Divisions (Kibakwe, Mpwapwa, Rudi) in the district will be selected by simple random sampling. A list of all villages in the selected divisions will be compiled, and villages found to have an on-going intervention or project will be excluded. Eighteen villages will be selected from the list by simple random sampling. The preselected villages will be listed alphabetically. A simple randomisation with a 1:1 allocation will be used to randomise villages to either control or intervention group. A list of random numbers will be generated in MS Excel 2007 and the generated values will be fixed by copying them as “values” next to the alphabetic list of the preselected villages. These will then be arranged in ascending order according to the generated random numbers: and the first 9 will be selected as intervention clusters and the last 9 as control clusters.

Generation of allocation sequence and randomisation of clusters will be done by a statistician blinded to study groups and not participating in the research. Data collectors will be masked of the village allocation by not informing them of the allocation, not being part of trial implementers and not being residents in any of the villages. However, trial participants may know if they are in the intervention or control group.

### Sample size estimate

The sample size was calculated for unmatched cluster-randomised trials [41] as follows:

whereby: **c** is the number of clusters required in each treatment group; **Z**_**α/2**_ is the standard normal distribution corresponding to the 95% degree of confidence on a two-sided test; **Z**_**β**_ is the standard normal distribution corresponding to 80% power; **σ**_**0**_ and **σ**_**1**_ are the within cluster standard deviations of the outcome variable in the presence and absence of intervention, respectively; **n** is the minimum number of individuals sampled in each cluster; **k** is the coefficient of variation of true means between clusters within each group; and **μ**_**0**_ and **μ**_**1**_ are the within cluster population means in the presence and absence of intervention, respectively.

As there is no information available on the intra-cluster coefficient of variation, the estimate for the between-cluster coefficient of variation (k) was based on conservative estimates of ≤0.25 and 0.15-0.25 experienced in similar health and nutrition studies [41, 42]. A coefficient of variation between clusters (k) of 0.1 was assumed and 30 infants per cluster based on district’s estimates of birth rates. Data from the 2009 formative survey were used to make assumptions on change of values of the primary outcome length-for-age Z-scores (LAZ): a mean LAZ of −1.5 and a standard deviation of 1.3 in the control group. From the formula, 8.9 (~9) clusters will be needed to detect at least a 0.35 difference in LAZ between intervention and control groups, with the power of 80% (Z_β_ = 0.84) and a statistical significance of 5% (p < 0.05; Z_α/2_ = 1.96, two-tailed test). A total of 270 infants will be enrolled in each study group. Allowing for a 10% loss to follow-up, a sample size of 297 infants, i.e. 33 per village, will be required. A total of 594 (~600) infants will be recruited.

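### The sample size uses k = 0.1, below the 0.15–0.25 range cited as its conservative basis, and the stated 80% power does not hold in that range

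*Protocol article*

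**What the plan says.** All of this is in the protocol article, mainly under Sample size estimate. That section says no intra-cluster information was available, so k "was based on conservative estimates of ≤0.25 and 0.15-0.25 experienced in similar health and nutrition studies". The next sentence reads "A coefficient of variation between clusters (k) of 0.1 was assumed and 30 infants per cluster". No reason is offered for moving from the cited values to 0.1.

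The other inputs are "a mean LAZ of −1.5 and a standard deviation of 1.3 in the control group", taken from the 2009 formative survey, two-sided 5% significance (Z = 1.96) and 80% power (Z = 0.84). The aim is "to detect at least a 0.35 difference in LAZ between intervention and control groups". The stated result is 8.9 clusters, rounded to 9 per group. Sampling and randomisation fixes the allocation: "the first 9 will be selected as intervention clusters and the last 9 as control clusters".

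**The concern.** In the unmatched-cluster formula the required number of clusters rises with k squared, so a smaller k is the favourable choice. A conservative planning value would sit at the cautious end of the evidence. Here the section calls its evidence conservative and then uses a number smaller than anything in the 0.15–0.25 interval.

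With nine villages per arm, between-village variance is a large part of the error. If k is really in the cited range, a true 0.35 LAZ effect would be missed far more often than the one time in five that 80% power implies. A null result could then be read as evidence that the package does not work.

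**Working it through.** **Inputs.** From Sample size estimate: n = 30 per village; control mean −1.5; SD 1.3 (control group); difference 0.35, so intervention mean −1.15; Z values 1.96 and 0.84. From Sampling and randomisation: 9 villages per arm. The intervention-group SD is not stated; I take 1.3 and then vary it.

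**Formula.** The equation is not in the text I have. The symbols defined around it match the standard unmatched formula for means:

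c = 1 + (1.96 + 0.84)² × V / 0.35², with V = (σ₀² + σ₁²)/n + k²(μ₀² + μ₁²)

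Power with 9 villages per arm = Φ(0.35 / √(V/8) − 1.96).

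**Fixed parts.**
- Within-village term: (1.69 + 1.69)/30 = 0.11267
- Sum of squared means: 2.25 + 1.3225 = 3.5725
- (2.8)²/0.35² = 7.84/0.1225 = 64

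**The plan's own figure (k = 0.10).** V = 0.11267 + 0.01 × 3.5725 = 0.14839, so c = 1 + 64 × 0.14839 = 10.5, not 8.9. Without the +1 it is 9.5. Power with 9 per arm is Φ(2.570 − 1.96) = 72.9%, or 77.8% without the +1. The stated 8.9 therefore does not reproduce from the stated inputs. With n = 30 and the +1, it returns if the intervention SD is about 0.97: V = (1.69 + 0.9409)/30 + 0.035725 = 0.12342, c = 8.90, power 80.5%.

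**Across the cited range (SD 1.3 in both arms).**

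| k | V | Clusters per arm for 80% | Power with 9 per arm | Detectable difference at 80% |
|---|---|---|---|---|
| 0.10 | 0.14839 | 10.5 | 73% | 0.38 |
| 0.15 | 0.19305 | 13.4 | 62% | 0.43 |
| 0.20 | 0.25557 | 17.4 | 50% | 0.49 |
| 0.25 | 0.33595 | 22.5 | 40% | 0.55 |

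The detectable difference d solves d = 2.8 × √(V/8), with the intervention mean set to −1.5 + d inside V.

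**Sensitivity of power from k = 0.15 to k = 0.25.**
- Intervention SD 0.97 (calibrated to 8.9): 67.5% to 42.7%
- No +1, SD 1.3: 66.6% to 44.1%
- t-test on 16 df, SD 1.3: 61.2% to 39.9%
- Most favourable combination tried (n = 33, SD 0.97, no +1): 74.7% at k = 0.15

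No variant reaches 80% at k = 0.15 or above.

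**The case against.** Four points on the other side have weight.

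1. The section cites two bases, and 0.1 satisfies the first, an upper bound of 0.25. A reader might infer that the plan's own sources contradict 0.1. The documents do not support that: the cited studies cannot be seen here, and it is unknown whether their values concern LAZ. What stands is narrower. Lying under an upper bound does not make a value conservative, and the second cited basis excludes it.

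2. Not all of the gap from 80% belongs to k. On the stated inputs power is already about 73% at k = 0.1, and the intervention SD is not given.

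3. A reader might infer that the trial's real power is 40–62%. That goes too far. The primary outcome is change in LAZ, and Data management and analysis plans mixed models with covariate adjustment. As an illustration, assume a baseline-to-endline correlation r acting equally at village and child level, so that the variance scales by 2(1 − r). For r from 0.5 to 0.8, power runs from about 62% to 95% at k = 0.15 and from 40% to 77% at k = 0.25; below 0.5 it is worse. The documents give no r, and the plan's calculation takes no credit for one.

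4. A reader might also take the Background figures, "Results of the surveys indicated high prevalence of stunting; 34% in 2009 and 59% in 2010", to mean that the planning mean should be near −2.3, so that even k = 0.1 falls well short. That needs an assumed age match between the 2010 infants and the 12- and 15-month visits, normality, and SD 1.3. It also holds k fixed while the mean moves, which by itself inflates the between-village SD from 0.15 to about 0.23. The documents establish none of this.

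**Conclusion.** The point holds as an unexplained inconsistency with a material consequence. The value k = 0.1 is below the 0.15–0.25 range offered as its conservative basis, and the stated 80% power is not sustained anywhere in that range. With SD 1.3 in both arms, power is about 62% to 40% and the requirement is 13.4 to 22.5 clusters per arm; with the intervention SD calibrated to the stated 8.9, power is about 68% to 43%. The size depends on the standard formula, the assumed intervention SD and an analysis of unadjusted cross-sectional LAZ. It is a sensitivity range for the plan's own calculation, not an estimate of power for the declared change-in-LAZ analysis.

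**What to change.** Keep 9 villages per arm. In Sample size estimate:

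- Give the reason for k = 0.1, or replace it with a value from the cited range.
- State the intervention SD that was used.
- Replace the single 80% figure with power and detectable difference across k = 0.10 to 0.25: on the assumptions above, about 0.38 LAZ at 0.10, 0.43 at 0.15 and 0.55 at 0.25.
- Say that these figures apply to unadjusted cross-sectional LAZ and that baseline adjustment could change them.
- If the 2009–2010 survey kept village identifiers, report the between-village SD or ICC of LAZ from it. The section says no intra-cluster information was available, so this may not be possible.

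The cost is a few sentences and a small table, plus a short survey analysis if the data allow. The downside is a less favourable stated power.

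### The 10% loss allowance is added to 270 instead of being divided out, so 297 per arm, 33 per village and 594 in total cover about 9.1% loss; the printed ~600 is the figure that fits

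*Protocol article*

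**What the plan says.** All the figures stand in one paragraph of the protocol article, under Sample size estimate.

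- Cluster size and between-village variation: "A coefficient of variation between clusters (k) of 0.1 was assumed and 30 infants per cluster". In the list of symbols, n "is the minimum number of individuals sampled in each cluster".
- Number of clusters per arm: "8.9 (~9) clusters will be needed to detect at least a 0.35 difference in LAZ between intervention and control groups".
- Number per arm before any allowance: "A total of 270 infants will be enrolled in each study group".
- Allowance for loss: "Allowing for a 10% loss to follow-up, a sample size of 297 infants, i.e. 33 per village, will be required".
- Total: "A total of 594 (~600) infants will be recruited".

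The 270 is 9 villages x 30 infants, so it is the number on which the calculation rests. The 297, 33 and 594 are that requirement after the loss allowance.

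**The concern.** An allowance for loss should ensure that the number still under observation at the end equals the number used in the calculation. The expected loss is a proportion of the infants recruited, so the required number must be divided by one minus that proportion. Multiplying by one plus the proportion gives a slightly smaller figure. Here the inputs (270 and 10%) and the outputs (297 and 33) are all printed, and the outputs do not follow from the inputs.

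What is at stake is the consistency of a stated target. A trial that recruited exactly 297 per arm and lost exactly the 10% it planned for would end below its own 270. The paragraph also leaves unclear which total is the target. Both 594 and ~600 are given, and only 600 meets the 10% allowance.

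**Working it through.** **Inputs**, all from Sample size estimate: 30 infants per village, 9 villages per arm, 270 per arm, 10% loss, 297 per arm, 33 per village, 594 (~600) in total, 8.9 clusters rounded to 9, difference 0.35 LAZ, control mean −1.5, SD 1.3, k = 0.1, Z values 1.96 and 0.84.

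**1. Reproducing the plan's figures.** Required number x (1 + loss):
- 270 x 1.10 = 297
- 30 x 1.10 = 33
- 2 x 297 = 594, and 18 x 33 = 594

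All are exact, so the allowance was added.

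**2. What remains after a 10% loss.** Recruited x (1 − loss):
- 297 x 0.9 = 267.3 per arm, which is 2.7 short of 270
- 33 x 0.9 = 29.7 per village, which is 0.3 short of 30
- 594 x 0.9 = 534.6 in total, against 540

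**3. Loss that the stated figures do cover.** 1 − 270/297 = 27/297 = 9.1%.

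**4. Dividing instead.** Required number / (1 − loss):
- 270/0.9 = 300 per arm, 600 in total
- 30/0.9 = 33.3 per village on average
- Check: 600 x 0.9 = 540 = 2 x 270

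If every single village had to keep 30, the figure would be 34 per village: 9 x 34 = 306 per arm, 612 in total.

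**5. Effect on the number of clusters, taking 8.9 at face value.** Only the within-village part of the variance depends on n. Lowering n from 30 to 29.7 can therefore raise the required clusters by a factor of at most 30/29.7 = 1.0101, and 8.9 x 1.0101 = 8.99, still under 9. With the plan's inputs the increase is smaller. The variance term, using an assumed SD of 1.3 in both arms and an intervention mean of −1.5 + 0.35 = −1.15, is:
- n = 30: (1.3² + 1.3²)/30 + 0.1² x (1.5² + 1.15²) = 0.1127 + 0.0357 = 0.1484
- n = 29.7: 0.1138 + 0.0357 = 0.1495

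The ratio is about 1.008, and 8.9 x 1.008 is about 8.97. If the printed 8.9 stood for a value as high as 8.95, the result would be about 9.02, a trivial excess.

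**6. Effect on power.** The formula is not shown in the text available, so its usual form for unmatched cluster trials is an assumption. For 9 villages per arm, power = Φ(√[m x 0.35² / variance term] − 1.96), with m = 9 if the formula has no added cluster and m = 8 if it adds one:

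| n per village | m = 9 | m = 8 |
|---|---|---|
| 30 | 77.8% | 72.9% |
| 29.7 | 77.5% | 72.6% |

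The difference is about 0.3 percentage points either way. Both columns lie below 80% because, under this assumed form, n = 30 calls for 7.84 x 0.1484/0.1225 = 9.5 clusters (10.5 with one added), not 8.9. That is a separate question about the 8.9. It adds no weight to the point about the loss allowance.

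**The case against.** The strongest reply is that the paragraph largely repairs itself. It ends at ~600, and 600 recruited with 10% lost leaves exactly the 540 that the calculation uses. This stands, and it is why no additional recruitment beyond the printed figure is needed. It does not remove the error, because ~600 is offered as a rounding of 594, while the figures called required remain 297 and 33.

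A second reply is that 270 already contains a rounding up. The formula's 8.9 clusters at 30 infants is 8.9 x 30 = 267 per arm, and 267.3 remain after a 10% loss from 297. This also stands, provided the 8.9 is taken as printed.

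A third reply is that 2.7 infants per arm is far smaller than the uncertainty in the assumed inputs, such as the cluster size, which comes from district birth-rate estimates. That is correct and limits the point to one of wording.

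A reader might infer that 33 is a quota at which recruitment in a village stops, so that the shortfall is built into fieldwork. The article does not say so. It gives 33 as the number required. Under Recruitment and collection of baseline information it describes a door-to-door search for all six-month-old infants, with consenting eligible infants enrolled, and sets no stopping number. A reader might also infer that the allowance leaves the trial underpowered. Steps 5 and 6 of the working do not support that.

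**Conclusion.** The error is real and small. The figures stated as required (297 per arm, 33 per village, 594 in total) result from adding 10% and cover a loss of about 9.1%. At the plan's own 10% they leave about 267 per arm and 29.7 per village, against 270 and 30. The total of ~600 printed alongside them is the one that satisfies the allowance.

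The arithmetic on recruitment rests only on printed figures and on reading loss to follow-up as a share of those recruited. The statement that the ninth village absorbs the shortfall rests on the printed 8.9. The power difference of about 0.3 points rests on an assumed formula, an SD of 1.3 in both arms and an intervention mean of −1.15. No conclusion about the adequacy of the design follows from this point.

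**What to change.** Either of two edits to Sample size estimate is enough:

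1. State the target as 300 infants per arm and 600 in total, an average of 33.3 per village, leaving 270 per arm after a 10% loss. In whole numbers this could be six villages of 33 and three of 34 per arm (6 x 33 + 3 x 34 = 300).
2. Keep 297, 33 and 594, and say that they allow for about 9% loss, or that about 267 per arm remain at 10%.

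In the same edit, describe 270 as the number per arm needed at follow-up rather than the number enrolled, since the next sentence asks for 297, and give one total instead of two.

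The cost is wording only. Because ~600 is already printed, the first option adds 600 − 594 = 6 infants to the exact figure and none to the rounded one.
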